###### Missing Data and Software

Every effort was made to minimize the number of missing data. If there are still missing data points, these will be replaced at T0 by the mean of the available data in each group (intervention or control group).

Statistical analysis will be carried out using R software (version 4.5.3; R Foundation for Statistical Computing)) [74].

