### Data Analysis

#### Quantitative Analysis

##### Number of Subjects

As this is a pilot study, the number of participating departments (N=8) and the number of professionals studied (15 professionals per department; N=120) were not determined by a power calculation [70] but by the operational constraints of the study, notably the maximum number of subjects recommended by the MM trainer for a group of meditative practice [55,71,72].

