###### Analysis of the Primary Outcome

For each individual, the psychological flourishing at work was measured (using EEPMT-13) at 2 time points: T0 and T3. Since each individual has 2 measures, and each individual belongs to a given department, we will use a multilevel model for the analysis of the primary outcome [73]. These models, also known as mixed models, are particularly well-suited to the analysis of this type of hierarchical data (ie, first level=the measure, second level=the individual, and third level=the department).

Noting Y_ijk_ as the EEPMT-13 measure j of individual i in department k, we obtain the following model 1 equation:

$$Y_{ijk}=\beta_{0}Z_{k}+u_{ik}+v_{k}+\beta_{1}{\;}^{*}X_{ijk}+\beta_{2}X_{ijk}G_{k}+e_{ijk}$$

where u_ik_, v_k_, and e_ijk_ are, respectively, the individual random effect (individuals having greater or lesser flourishing), the department random effect (certain departments presenting on average greater or lesser levels of flourishing), and the residual deviation of the ijk measure; Z_k_ is a vector of binary indicator variables indicating the department type of department k; G_k_ is an indicator variable for the intervention group (0 if the department belongs to the control group and 1 if the department has received the intervention); X_ijk_ is a measurement time indicator variable (0 if the measurement is taken at T0 and 1 if it is carried out at T3).

With this coding, the 4 fixed parameters making up the β_0_ vector provide mean levels according to the department type (which is a stratification factor in randomization), the parameter β_1_ corresponds to the variation between T0 and T3 for departments belonging to the control group, and β_1_ + β_2_ corresponds to the variation between T0 and T3 for departments belonging to the intervention group. The parameter β_2_ thus corresponds to the parameter of interest that describes the effect of the intervention, and the main hypotheses tested will be as follows:

H0: evolution between T0 and T3 is identical between the 2 groups (ie, β_2_=0)

H1: evolution between T0 and T3 is not identical between the 2 groups (ie, β_2_≠0)

This test will be performed using the Wald test (2-tailed test, type I error rate=5%).

It will be investigated whether a residual effect of the intervention persists at T4, by analyzing the 2 measurements at T0 and T4 in a model similar to model 1.

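### Filling missing T0 scores with the arm mean puts constant pseudo-outcomes into Model 1, which needs no fill; the harm is small unless many T0 scores are missing

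*Protocol article*

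**What the plan says.** Under Missing Data and Software, the protocol article covers whatever gaps are left after data collection ("If there are still missing data points") with a single rule: "these will be replaced at T0 by the mean of the available data in each group (intervention or control group". The primary outcome is not exempted, no multiple imputation is mentioned, and nothing is said about allowing for the fact that filled values were not observed. The rule is confined to T0; no fill is stated for T3 or T4.

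Under Analysis of the Primary Outcome: "Since each individual has 2 measures, and each individual belongs to a given department, we will use a multilevel model". The time indicator is "0 if the measurement is taken at T0 and 1 if it is carried out at T3", so the T0 score is one of the two responses per person. The fixed part has four department-type means, a time effect and a time-by-group effect. There is no group term at T0. The random part has "the individual random effect (individuals having greater or lesser flourishing), the department random effect" and a residual. The coefficient β2 "thus corresponds to the parameter of interest that describes the effect of the intervention" and is tested by a two-sided 5% Wald test. A model of the same kind is planned for T0 and T4.

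The planned size is "15 professionals per department; N=120"; the Results section reports 108 enrolled. No expected proportion of missing T0 scores is given.

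**The concern.** Replacing a missing baseline covariate by a mean can be defended in a randomised trial. That defence does not carry over here, because T0 sits on the left-hand side of Model 1. The filled values are treated as measured outcomes but carry neither the person's own deviation nor a residual.

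Two consequences follow. The estimated variance components and within-person correlation are distorted, and the model uses that correlation to weight everyone's T0 against their T3. The estimate of β2 can also become less precise while its reported standard error does not grow to match, which makes the Wald test somewhat too liberal. The variance components matter in their own right, since the Discussion looks ahead to a larger study for which they would be natural planning inputs.

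**Working it through.** **1. The plan's own figures.** 8 departments × 15 = 120, as stated. Enrolment of 108 gives 108/8 = 13.5 per department, so the simulations use 13 and 15 per department (N = 104 and 120). The article gives no SD, effect size or power to reproduce.

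**2. What a filled value is under Model 1.** For person i in department k, Model 1 describes T0 as (mean of the department type) + v_k + u_ik + e. The fill is the mean of the observed T0 scores in the arm, that is, over four departments of four different types. So:
- the type mean and v_k are replaced by an average over types and departments;
- u_ik and e are set to nothing;
- the constant differs between arms, whereas Model 1 gives both arms the same T0 mean within a department type.

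Without the fill, a participant with only T3 still contributes that score to the likelihood.

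**3. Effect on the correlation, by arithmetic.** Let p be the share with T0 missing (all having T3), q the share with T3 missing among those with T0, and ρ the true within-person correlation within department. Among those with T3, the share with a filled T0 is p′ = p / [p + (1−p)(1−q)]. The covariance shrinks by (1−p′) and the average of the two variances by about (1−p/2), so the estimated correlation is about ρ(1−p′)/(1−p/2). With ρ = 0.7 and q = 0.10:
- p = 0.05: p′ = 0.05/0.905 = 0.055; 0.7 × 0.945/0.975 = 0.678 (simulated 0.676)
- p = 0.10: p′ = 0.10/0.91 = 0.110; 0.7 × 0.890/0.95 = 0.656 (simulated 0.654)
- p = 0.20: p′ = 0.20/0.92 = 0.217; 0.7 × 0.783/0.90 = 0.609 (simulated 0.609)

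**4. Effect on β2, by simulation.** Model 1 was fitted by REML under β2 = 0, rejecting when |z| > 1.96, with 1,000 runs per setting. Each data set was analysed with available data only and again with the arm-mean fill. Assumptions not in the article: total SD 1, department ICC 0.05, equal type means, no department-by-time variation, missing completely at random, and the missing rates and ρ shown. With T0 complete, rejection was 4.9% to 6.4%, so the set-up roughly reproduces the nominal 5%.

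Each cell gives available data / arm-mean fill.

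| N | ρ | T0 missing | T3 missing | Estimated correlation | Mean SE ÷ true SD | True SD of β2 | Rejection |
|---|---|---|---|---|---|---|---|
| 120 | 0.7 | 5% | 10% | 0.70 / 0.68 | 0.967 / 0.948 | 0.143 / 0.146 | 6.7% / 7.1% |
| 120 | 0.5 | 10% | 10% | 0.49 / 0.46 | 0.989 / 0.961 | 0.175 / 0.175 | 5.3% / 6.2% |
| 120 | 0.7 | 10% | 10% | 0.70 / 0.65 | 0.978 / 0.929 | 0.144 / 0.151 | 5.9% / 7.0% |
| 104 | 0.7 | 10% | 20% | 0.69 / 0.65 | 0.966 / 0.930 | 0.165 / 0.171 | 5.7% / 6.8% |
| 120 | 0.5 | 20% | 10% | 0.49 / 0.43 | 0.970 / 0.900 | 0.182 / 0.185 | 6.0% / 7.9% |
| 120 | 0.7 | 20% | 10% | 0.70 / 0.61 | 0.983 / 0.897 | 0.148 / 0.160 | 5.7% / 8.5% |
| 120 | 0.8 | 20% | 10% | 0.80 / 0.69 | 0.953 / 0.887 | 0.129 / 0.145 | 6.8% / 8.1% |
| 104 | 0.7 | 30% | 10% | 0.70 / 0.56 | 0.977 / 0.850 | 0.164 / 0.184 | 6.1% / 9.4% |

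Simulation error on one rejection rate is about √(0.06 × 0.94/1000) = 0.75 points, and on one true SD about 1/√2000 = 2.2%.

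**5. The part due to the fill.** The available-data SE is itself slightly short of the true SD, so the fair measure is the ratio of the two SE ÷ SD values.
- 5% missing: 0.948/0.967 = 0.98, a 2% shortfall.
- 10% missing: 0.961/0.989 = 0.97, 0.929/0.978 = 0.95 and 0.930/0.966 = 0.96, a 3 to 5% shortfall.
- 20% missing: 0.900/0.970 = 0.93, 0.897/0.983 = 0.91 and 0.887/0.953 = 0.93, a 7 to 9% shortfall.

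At 20% the true SD of β2 rises by 2% at ρ = 0.5 (0.1853/0.1815), 8% at 0.7 (0.1600/0.1478) and 13% at 0.8 (0.1453/0.1287). At ρ = 0.7 the reported SE even falls slightly, from 0.1453 to 0.1436.

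**6. Further runs.** With 108 people, ρ = 0.7, 15% of T3 missing and 600 runs, SE ÷ SD was 0.981 either way at 2% missing T0. It was 0.975 against 0.947 at 5%, and 0.978 against 0.940 at 10%. Rejection was 6.7% against 6.3% at 5% and 5.7% against 6.2% at 10%. With 104 people and 250 runs, SE ÷ SD differed by less than 0.01 at 5 to 10% missing, and at 20% it was 0.94 against 0.87 (0.87/0.94 = 0.93).

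**The case against.** The strongest reply is that few T0 scores will be missing. T0 is collected at the inclusion visit, before the participant knows the department's allocation, and a dedicated research associate handles the quantitative data in an electronic case report form. At 2% missing the fill makes no visible difference, and at 10% or less the shift in rejection is about a point or less, close to simulation error. The study is also an exploratory pilot without confirmatory scope, not sized by power, whose associations are to be read with caution. All of this stands and limits the size. It does not make the rule right: with few gaps the fill brings no benefit, and with many it does harm.

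It may also be said that the rule was meant for descriptive tables only. The article does not say so.

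A reader might infer more than the documents support:
- **That β2 is biased.** The simulations assume data missing completely at random, where no bias is expected. Missingness depending on department or on T3 was not tested.
- **That the whole gap between SE and true SD comes from the fill.** At 20% missing and ρ = 0.7 the gap is about 10%, but about 2% is there without any fill.
- **That T3 is mean-filled too.** The sentence is confined to T0.

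**Conclusion.** The rule is wrong as written, with small impact if T0 forms are nearly complete. The conflict with Model 1 and the weakened correlation follow from the article's own text and simple arithmetic. The effect on inference depends on a T0 missing rate that the article does not give.

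Up to 10% missing, the effect on the SE and the Wald test is negligible to minor. The 20% case is a stress test, not an expectation: an SE about 7 to 9% too small relative to the available-data analysis, a true SD of β2 about 2 to 13% larger depending on ρ, and rejection of 7.9 to 8.5% against 5.7 to 6.8%.

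These figures take Model 1 as true, with an assumed department ICC of 0.05 and ρ of 0.5 to 0.8. Because the simulations set the four type means equal, they do not include any further distortion from averaging over types that differ. The documents do not support a claim that the pilot's conclusions would be overturned.

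**What to change.** Delete the T0 mean replacement for the model-based analyses. State instead that Model 1 is fitted by REML to all available T0 and T3 EEPMT-13 measures of every enrolled participant with at least one of them, and that the T4 model is fitted in the same way to all available T0 and T4 measures. Report the number of missing T0 scores by arm and department.

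Keep the two-time-point models as specified. Pooling T0, T3 and T4 in one model would need new time and interaction terms, which this defect does not call for. Multilevel multiple imputation using department, department type, arm and the other time point is optional as a sensitivity analysis.

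The change removes a step and needs no new data. The article says the analysis is in progress, so the change should be dated and disclosed as an amendment to the analysis before results are reported.

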### Qualitative Data Analysis

#### Data Management and Analysis

Pseudonymized transcripts will be produced. Qualitative data will be systematically coded. Triangulation of coding will be conducted for the initial FG and interviews to ensure consistency in coding.

#### Deductive and Inductive Analysis

Data from FG and individual interviews will undergo thematic content analysis (MAXQDA 2020 software [75]). Analyses will follow a deductive approach (based on the themes from the data collection guides), followed by an inductive approach (developing new categories to account for all collected data), with iteration. The analysis will consider 4 levels: individual, team or department, organization or hospital, and the external hospital context (health care system). Data collected through observations will be analyzed and used to contextualize the analysis of FG and interview data and to triangulate the findings. Qualitative data will be analyzed using a combined deductive-inductive approach within a realist evaluation framework. A theoretical framework of intervention implementation will inform the initial coding structure, which will be subsequently refined inductively to incorporate data generated beyond predefined categories. Reflexivity will be ensured through field notes and iterative multidisciplinary team discussions, enhancing credibility and confirmability. Reliability will be reinforced using qualitative data analysis software, ensuring traceability of the analytic process and supporting confirmability [76].

### Integration of Findings

Qualitative and quantitative data will be analyzed separately. Integration will be performed subsequently to identify points of convergence and divergence and to generate hypotheses for further analysis. We will apply a table of convergences and divergences between the results, the interpretation of which will be discussed by the interdisciplinary team and compared to the literature. Feasibility as an outcome will be evaluated according to an overall informed decision-making framework [44], based on prespecified indicators and conclusions based on a realist approach: exploratory outcomes of the intervention, feasibility, and barriers and facilitators identified for each context; consistency with the theoretical logic model; and potential for organizational adaptation. They will be analyzed in each department context to inform trends and assess the barriers and facilitators to inform future scalability. This integrated analysis, rather than isolating the components, will provide a more comprehensive assessment of effectiveness, feasibility, and implementation.

### Ethical Considerations

This study was approved by the Sud-Est VI ethics committee (Clermont Ferrand, France) and the French national data protection authority (*Commission nationale de l’informatique et des libertés*, CNIL). The study was registered on ClinicalTrials.gov (NCT06331065). Written informed consent was obtained from participants, as required by French law for this type of study. All participants were informed of the study objectives and data confidentiality. Information was provided to the HCL Social and Economic Committee training group.

This protocol has been described in compliance with the SPIRIT (Standard Protocol Items: Recommendations for Interventional Trials) 2025 checklist (Checklist 1) [77].

## Results

The PROMIND study was funded in October 2021, and the funding was extended in June 2024. This study was conducted from May 2024 to June 2025. In total, 108 participants were enrolled in the study; data collection ended on June 30, 2025. Data analysis is in progress. After data analysis, the COPR will be asked to discuss the results and prospects for implementing MM based on the study findings. Workers’ representatives will be informed of the results. A dedicated meeting to summarize and discuss the results of PROMIND will be planned with the participants.

We expect the results of this study to be published by the end of 2026. Scientific publications and communications (national and international) will be planned to publicize this trial and its findings in the fields of psychiatry, public health, and occupational health. Recommendations for publication in the field of epidemiology and realist evaluation will be followed.

## Discussion

### Principal Findings

This study expects that the co-constructed workplace-based mindfulness intervention is an acceptable and relevant intervention for French hospital professionals: we hypothesize that the implementation of this MBI improves psychological flourishing in the workplace in 4 hospital departments in comparison with a geographical control and, more broadly, mental health at work at the individual and collective levels. With the intervention modalities chosen in accordance with the intervention mapping protocol [53], we expect that this improves the relevance of the study and the feasibility of its implementation.

The originality of the PROMIND study is the adoption of a structured approach to intervention planning in mental health promotion for hospital professionals. The strengths of this innovative study lie in the improvement strategies employed, including the co-construction, and the collective approach to the intervention and to the MM program within a team that usually works together (department) [78]. Moreover, this MBI is a multiprofessional training course that also transmits practical resources and is prepared as an organizational intervention, taking into consideration the views of professionals, which is conducive to team effectiveness [79]. The participatory development with stakeholders is one of the recommendations for promoting the feasibility of implementation, the relevance, and ultimately the sustainability of the proposed intervention [44,53]. The initial co-construction step enabled the emergence of local “ambassadors” within the participating departments involved in relaying study information and their motivation; the identification of main MBI components, such as professional time that could be allocated to training (eg, interval and duration of sessions); and the communication strategies to support participation. This also facilitated the support and practical involvement of hospital executive management throughout the study, and it is known that culture and infrastructure also improve feasibility [45]. In addition, a reduced duration of practice sessions was chosen for this MBI adapted for hospital professionals. While brief interventions can facilitate access to a meditation training program, the dose proposed must be sufficient to ensure effectiveness [41] and requires specific evaluation.

The innovative feature of this study is the adoption of a mixed evaluation methodology. The methodological pluralism is based on a randomized controlled pilot study with a complementary approach of realist evaluation, due to the complex nature of the intervention [44]. Intervention epidemiology raises the challenge of choosing a primary outcome, whereas mental health is a complex domain, which requires the use of several questionnaires for a reliable assessment. The EEPMT-13 is an innovative tool to specifically explore mental health in the workplace, which requires further exploration. The focus of the evaluation on positive mental health opens up a viewpoint that complements the approaches to distress at work, to adopt a broader view of mental health as a continuum [80,81]. Most studies investigating MM among hospital professionals investigate burnout using questionnaires such as the Maslach Burnout Inventory Scale as a specific tool for assessing distress in the workplace [41]. However, some consider that it is not based on a solid theoretical model and that the construction of certain items is questionable [82]. Otherwise, they use non–workplace-specific and routine mental health assessment criteria (eg, anxiety, stress, and quality of life) [41]. The complementary realist evaluation approach provides a deeper and sharp understanding of this complex domain at the individual and organization levels and in the patient care relationship [59]. Although this pilot study may not provide conclusive evidence, it will provide useful knowledge on how these interventions work in a real-world hospital setting and on the extent to which MM can promote mental health in an organizational environment with psychosocial risk factors. Finally, this mixed methods design is especially appropriate for pilot studies of complex interventions where the exploratory primary outcome of effectiveness as well as feasibility and processes must be explored.

### Limitations

In this pilot study, inclusion was limited to hospital care departments. However, hospitals include technical and administrative departments with specific needs that may require adaptation of the intervention. This will require a new dedicated study. In addition, while all willing professionals from participating departments can be included, only part of the team can participate in the MM program because the number of people is limited per group (n=15). Moderately sized groups are therefore usual in MBI, and group size varies according to the program and practice contexts [55,71,72]. This limits the potential impact of MBI on the departments and work organization, which will be assessed through realist evaluation. In a larger-scale study, it may be interesting to train more professionals at the same time in each department, based on the evaluations of this pilot study. It would also be important to include more departments in a larger-scale study. Indeed, in this pilot study, only 2 groups comprising 4 departments each could be included. Any associations identified in this study should therefore be interpreted with caution due to the risk of bias and will need to be confirmed during the scalability stage. Furthermore, the demands associated with the mixed methods evaluation in the study, particularly in terms of the time required, complicate the implementation of an intervention among a specific population for whom the issue of availability and task prioritization is a major concern. The self-administered questionnaires may induce a desirability bias [83]. However, the quantitative assessment is fast. In addition, the self-administered questionnaires can reduce anxiety during the assessment and investigate behaviors that are difficult to observe in other ways [84]. This pilot study has an open-label design, which may introduce bias. The delivery of the MM sessions by an external trainer limits the impact of the lack of blinding during the MM program.

### Conclusion

The results of this pilot study will provide essential data and input for the sustainable and larger-scale implementation of MBIs in the workplace, facilitating access to relevant, evidence-based interventions to support the mental health of hospital professionals. The challenges of implementation and evaluation of a workplace-based mindfulness intervention adapted to hospital professionals are multiple and complex; the use of a health program planning model such as the intervention mapping protocol is important for structuring the steps of co-construction, implementation, and evaluation of the intervention. Participative research and cooperation between hospital professionals, researchers, experts in MM, and the hospital management are essential to promote the success of initiatives such as this.
